### Participants

2.4

Patients with CID and healthy controls will be recruited through outpatient clinics and community channels, including WeChat and university campuses. Recruitment materials will describe the target population, eligibility criteria, intervention procedures, and contact details. Interested individuals will receive a study brochure and complete screening. Eligible patients will undergo baseline assessment and randomization, followed by assessments at baseline, week 4, and week 8. Healthy controls will undergo baseline clinical screening and baseline assessments before fNIRS acquisition.

### Recruitment and procedure

2.5

Recruitment will take place at Tongde Hospital of Zhejiang Province Affiliated to Zhejiang Chinese Medical University through outpatient clinics and online notices distributed via WeChat. Recruitment materials will describe the target population, eligibility criteria, intervention procedures, and contact details. Interested individuals will receive a study brochure and complete a screening form. Eligible patients with CID will then undergo baseline assessment and randomization. Outcome assessments will be conducted at baseline, week 4 (post-treatment), and week 8 (follow-up). Healthy controls will be recruited as a reference group for baseline fNIRS comparison only. Before fNIRS assessment, their eligibility will be verified through clinical interview and baseline assessments.

### Eligibility

2.6

#### Diagnostic criteria

2.6.1

CID will be diagnosed in accordance with the International Classification of Sleep Disorders, Third Edition (ICSD-3). Specifically, eligibility will require fulfillment of all of the following criteria:

Impairment in sleep initiation, sleep maintenance, and/or early-morning awakening.Symptom occurrence on at least three nights per week for a duration of ≥3 months.Absence of attribution of the insomnia-related complaints to other sleep disorders.

#### Eligibility criteria

2.6.2

Participants will be considered eligible for inclusion upon fulfillment of all of the following criteria:

Diagnosis of CID in accordance with the ICSD-3 diagnostic criteria, together with an ISI score of ≥10.Age between 18 and 70 years, with no sex-based restriction, and right-handedness.No use of medications or other therapeutic interventions for insomnia within 1 month prior to enrollment.Preserved ability for normal communication and compliance with study procedures.Written informed consent must be provided.

Healthy controls will be required to meet all of the following criteria:

Right-handed individuals of either sex, aged between 18 and 70 years;An ISI score ≤7, a Pittsburgh Sleep Quality Index (PSQI) score ≤5, and a HAMA score <7;No history of major chronic diseases or severe organic dysfunctions (e.g., cardiovascular, hepatic, or renal diseases);No use of hypnotics, antidepressants, central nervous system stimulants, or any other medications/substances known to substantially affect sleep architecture or central nervous system function within 1 month prior to enrollment;Voluntary provision of written informed consent prior to study participation.

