#### Exclusion criteria

2.6.3

Participants will be excluded upon fulfillment of any of the following criteria:

Presence of severe or unstable medical conditions, including cardiovascular or cerebrovascular disease, malignancy, nephritis, hematological disorders, other life-threatening diseases, or active infectious disease.Presence of severe depressive symptoms, defined as a Hamilton Depression Rating Scale (HAMD) score of >24.Presence of significant impairment in speech, language, or hearing, or the presence of cognitive or neurological disorders.Current substance abuse or severe dependence on alcohol or other psychoactive substances, or current exposure to medications or substances with substantial effects on sleep or central nervous system function, including antidepressants or central stimulants.Presence of secondary insomnia attributable to other organic diseases.Pregnancy or breastfeeding status.History of needle syncope or presence of skin damage at the intended acupuncture sites.Known allergy to metals, including acupuncture needles.Current participation in another clinical study.

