### Data analysis

2.11

All statistical analyses will be performed by an independent statistician using SPSS version 29.0 (IBM Corp., Armonk, NY, USA) and R software (version 4.3.x). The primary analysis will follow the intention-to-treat principle, including all randomized participants; per-protocol analysis will be used as sensitivity analysis. Continuous variables will be summarized as mean ± SD or median (IQR), and categorical variables as counts and percentages. Baseline characteristics will be summarized descriptively, with standardized mean differences used to assess group balance. No formal baseline hypothesis testing will be performed. Baseline fNIRS comparisons between patients with CID and healthy controls will use ANCOVA controlling for age, sex, BMI, caffeine/alcohol intake, and recording time.

Longitudinal continuous outcomes will be analyzed using linear mixed-effects models with fixed effects for group, time, and group-by-time interaction, and a random intercept for each participant. The main treatment effect will be the between-group difference in change from baseline to week 4; week 8 will be analyzed as follow-up. An unstructured covariance matrix will be attempted first; if convergence fails, AR(1) or compound symmetry structures will be considered based on model fit. Missing data will be handled under the missing-at-random assumption using multiple imputation by chained equations with 20 datasets. The imputation model will include treatment group, time, baseline and available follow-up values, and relevant variables such as age, sex, ISI, PSQI, and HAMA. Results will be pooled using Rubin’s rules.

This is a superiority trial. For ISI, the null hypothesis is no between-group difference in change from baseline to week 4; the alternative is greater improvement in the treatment group. A 3-point ISI difference will be used for sample-size estimation and clinical interpretation but not as a noninferiority or superiority margin. Because there are two primary endpoints, a two-sided Bonferroni-adjusted alpha of 0.025 will be used for each. Secondary outcomes and exploratory fNIRS endpoints will be adjusted using the false discovery rate method where appropriate.

Raw fNIRS data will be processed using NirMaster software (Znion, Wuhan, China). To ensure transparency and reproducibility, the data analysis pipeline will follow standard fNIRS processing procedures, structured into preprocessing, quality control, and feature extraction.

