## Discussion

3

CID places a substantial burden on both individuals and society. It can markedly impair quality of life and work performance (46) and has been associated with a higher risk of metabolic syndrome (47), hypertension (48), and diabetes (49). Persistent untreated insomnia has also been linked to psychiatric morbidity, particularly depression (50), and may contribute to reduced pain tolerance and impaired immune function (51, 52). In addition, insomnia is often accompanied by anxiety, substance misuse, and other psychological or behavioral problems, including suicidal behavior in severe cases (53, 54).

The conventional acupuncture prescription in this trial includes EX-HN1, EX-HN22, HT7, SP6, BL62, and KI6. It was selected by integrating traditional Chinese medicine theory, clinical experience, and contemporary evidence. In traditional theory, insomnia is related to disturbance of the Heart and Brain and may involve dysfunction of the Liver, Spleen, and Kidney. EX-HN1 and EX-HN22 are commonly used for head-related and sleep-related symptoms; HT7 is used to calm the mind; SP6 regulates yin-yang balance; and BL62/KI6 correspond to the Yangqiao and Yinqiao meridians, which are traditionally linked to sleep–wake regulation.

Systematic reviews of pattern-based acupuncture prescriptions for insomnia have reported that HT7, SP6, EX-HN22, and EX-HN1 are among the commonly selected acupoints in clinical studies (55). A systematic review of randomized controlled trials on primary insomnia has indicated that BL62 and KI6 constitute a frequently used acupoint combination in clinical practice (56). These findings suggest that the present prescription is consistent with the core acupoint-selection patterns observed in previous insomnia studies. In addition, mechanistic studies and reviews indicate that acupuncture at sleep-related points, particularly combinations involving HT7 and SP6, may be associated with modulation of autonomic activity, sleep-related neurotransmitters, neuroendocrine function, and central arousal networks (57, 58).

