The present study is designed as a pragmatic add-on superiority trial in which both groups receive standardized conventional acupuncture, with the treatment group receiving additional ultrasound-guided SG acupuncture. Accordingly, any observed between-group difference reflects the add-on effect of SG acupuncture within this context, rather than the isolated effect of either modality. Several limitations warrant consideration. First, this is a single-center trial with a modest sample size, which may limit generalizability; furthermore, given the absence of published effect-size data for ultrasound-guided SG acupuncture in CID, the sample was powered to detect a clinically meaningful add-on difference in ISI, and smaller neurofunctional effects may be underpowered. Second, the absence of a sham SG acupuncture or para-needling control precludes determination of stellate-ganglion target specificity and prevents full separation of specific physiological effects from nonspecific needling, expectancy, therapist–participant interaction, or ultrasound-related contextual factors. Third, the short follow-up duration (final assessment at week 8) leaves the long-term durability of treatment effects uncertain. Fourth, fNIRS-derived Oxy-Hb signals reflect local cortical hemodynamics rather than direct neural activity, and are subject to confounding by systemic vascular status or CID-related neurovascular alterations; Oxy-Hb changes should therefore not be equated with neural activation or used to draw definitive causal inferences. Relatedly, the verbal fluency task engages prefrontal executive-linguistic networks specifically and may be influenced by semantic memory, linguistic proficiency, and educational background; task-evoked fNIRS responses should thus be interpreted as domain-specific rather than as a generalized index of executive function. Finally, as no universally accepted protocol for SG acupuncture currently exists, the manipulation parameters adopted here are protocol-defined, and optimal stimulation intensity, frequency, and treatment course remain undetermined.

Future research should employ multicenter, sham-controlled designs with larger samples, longer follow-up periods, and objective sleep measurements to confirm and extend these findings.

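### Healthy controls face a stricter medical-history filter than patients, and the baseline fNIRS ANCOVA has no comorbidity term, so part of a CID-versus-control difference could reflect chronic disease rather than insomnia

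*Protocol article*

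**What the plan says.** **Controls.** Section 2.6.2 of the protocol article requires: "No history of major chronic diseases or severe organic dysfunctions (e.g., cardiovascular, hepatic, or renal diseases").

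**Patients.** The inclusion list in the same section sets no general-health requirement. Section 2.6.3 excludes for "Presence of severe or unstable medical conditions, including cardiovascular or cerebrovascular disease, malignancy, nephritis, hematological disorders" and some further conditions. It also excludes "Presence of secondary insomnia attributable to other organic diseases", which removes disease judged to cause the insomnia but not disease that merely coexists with it.

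**Use of the controls.** Section 2.5: "Healthy controls will be recruited as a reference group for baseline fNIRS comparison only".

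**Analysis.** Section 2.11 specifies for this contrast an "ANCOVA controlling for age, sex, BMI, caffeine/alcohol intake, and recording time". No blood pressure, vascular or metabolic comorbidity, or cardiovascular medication is in the list.

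**The protocol's own view of the signal and the disease.** The limitations paragraph of the Discussion says that Oxy-Hb signals "are subject to confounding by systemic vascular status or CID-related neurovascular alterations". The opening of the Discussion says that CID "has been associated with a higher risk of metabolic syndrome (47), hypertension (48), and diabetes (49").

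**The concern.** The two cohorts pass different medical filters. One rule looks at history, the other at present disease. One covers major chronic disease as such, the other is qualified by severity or instability. The factor filtered more strictly in controls is one that the protocol itself ties both to the outcome (Oxy-Hb) and to the condition under study (CID). That is the usual structure of confounding, and it is created here by the eligibility rules.

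At stake is the interpretation of the only comparison for which controls are recruited. The Introduction and Discussion intend it to describe brain function in CID and to find imaging features of the disease. With these filters, an altered prefrontal response in patients could come partly from vascular or metabolic disease, or its treatment, and be reported as a feature of insomnia.

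**Working it through.** **1. The rules side by side**

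| | Healthy controls (2.6.2) | Patients (2.6.2, 2.6.3) |
|---|---|---|
| Time frame | History | Presence |
| Threshold | Major chronic disease or severe organic dysfunction | Severe or unstable condition |
| Stable, treated chronic disease | Barred if it counts as major | Not clearly barred |
| Age range | 18–70 | 18–70 |

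The age range makes stable chronic disease among patients realistic. The article states no matching on comorbidity.

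**2. Illustrative size**

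The plan gives no figure to reproduce. It gives neither the prevalence of stable comorbidity in patients nor its effect on Oxy-Hb, so both are assumed.

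- *p* = proportion of patients with such disease, taken as 0 in controls (assumed).
- *g* = shift in the ROI beta due to the disease, in SD units (assumed).
- Spurious standardized difference with no insomnia effect: *d* = *p* × *g*.
- Standard error: √(1/n₁ + 1/n₂). The false-positive rate comes from the noncentral t distribution at two-sided 0.05 (assumed level).
- Sample sizes from section 2.3: 80 patients and 24 planned controls. A reduced case uses 64 (80 × 0.80) and 20, the stated minimum per group.

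| *p* | *g* | *d* | 64 vs 20 | 80 vs 24 |
|---|---|---|---|---|
| 0.10 | 0.3 | 0.03 | 5.2% | 5.2% |
| 0.20 | 0.3 | 0.06 | 5.6% | 5.8% |
| 0.30 | 0.5 | 0.15 | 8.9% | 9.8% |
| 0.40 | 0.8 | 0.32 | 23.5% | 27.5% |

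These rates are for an unadjusted two-sample test. Adjustment for age, sex and BMI would remove some of the shift, and the FDR correction planned for fNIRS comparisons would change the level.

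**3. Does a comorbidity covariate work when no control has the disease?**

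Yes. With a group term and a yes/no comorbidity term there are three cells: affected patients, unaffected patients and controls. Three parameters fit three means exactly. The comorbidity coefficient is estimated among patients, and the group coefficient equals the mean of unaffected patients minus the mean of controls, which is the restricted contrast.

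A simulation with 80 vs 24, *p* = 0.40, *g* = 0.8 and no insomnia effect confirmed this. The two estimates agreed to rounding error. False-positive rates were about 24% unadjusted, about 5% with the covariate and about 5% with restriction. (The unadjusted rate is a little below 27.5% because a mixture of affected and unaffected patients also has more variance.) With the other ANCOVA covariates in the model, the equality is approximate rather than exact.

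**4. Cost in precision**

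For 80 vs 24 the standard error is √(1/80 + 1/24) = 0.233 SD.

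- 20% of patients affected: √(1/64 + 1/24) = 0.239, or 2.8% higher.
- 40% affected: √(1/48 + 1/24) = 0.250, or 7.4% higher.

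Starting from 64 vs 20, the increases are 2.9% and 7.6%. The loss is small because the number of controls limits precision.

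**The case against.** **The eligibility gap may be narrower than it looks.** Section 2.6.3 can be read as naming whole disease classes, so that any cardiovascular disease is excluded in patients. Section 2.6.2 does not define which chronic diseases are major. A reader might infer that a patient with stable treated hypertension or diabetes definitely enters while a control with the same history definitely does not. The text makes that plausible but does not settle it. What remains is that presence is narrower than history, and that stable hypertension and diabetes are not clearly excluded in patients.

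**It is partly handled.** Age, sex and BMI carry some of the vascular difference. Section 2.8.3 has medication use documented at fNIRS assessment. The Discussion admits vascular confounding and warns against definitive causal inference. All of this stands. But the admission is general: it is not connected to the unequal filters, and no analysis follows from it.

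**Restriction changes the question.** If vascular change is partly a consequence of CID, a contrast limited to disease-free patients describes a narrower and less typical group. This is a fair point about the estimand. It is why both results should be shown rather than one replacing the other.

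**A reader might infer that no covariate can help**, since by design essentially no control has the disease. That is wrong for a yes/no term, as step 3 shows.

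**An analysis plan might deal with this.** The article fixes both the eligibility rules and the covariate list, so the point rests on stated text.

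**Conclusion.** The point holds as a modest, inexpensive improvement. As planned, the baseline CID-versus-control contrast can attribute to insomnia a difference that belongs partly to chronic comorbidity, along a path whose two links the protocol states itself. This rests on reading the patient rule as admitting at least some stable chronic disease that the control rule bars.

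The size is unknown. The illustrative range, from about 5% (essentially nominal) to about 28%, depends wholly on assumed prevalence and effect and should not be quoted as an estimate.

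A reader might infer that the primary results are compromised. They are not: both primary endpoints, ISI and Oxy-Hb change, are compared between randomized arms that share the same patient criteria.

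**What to change.** At the Week 0 clinical interview and physical examination, already scheduled in Table 1, record for each patient whether the healthy-control medical-history criterion is met. In section 2.11, do one of the following for the baseline contrast:

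- add this yes/no term to the ANCOVA; or
- report the contrast restricted to patients who meet the criterion.

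Report the all-patient contrast alongside, and attribute a difference to CID only if it persists in the like-for-like analysis. Patient eligibility for the randomized trial stays as it is.

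The cost is one item on the baseline form, a sentence or two in section 2.11, the small loss of precision shown in step 4 for this one contrast, and a narrower patient group behind the restricted result.

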#### Exclusion criteria

2.6.3

Participants will be excluded upon fulfillment of any of the following criteria:

Presence of severe or unstable medical conditions, including cardiovascular or cerebrovascular disease, malignancy, nephritis, hematological disorders, other life-threatening diseases, or active infectious disease.Presence of severe depressive symptoms, defined as a Hamilton Depression Rating Scale (HAMD) score of >24.Presence of significant impairment in speech, language, or hearing, or the presence of cognitive or neurological disorders.Current substance abuse or severe dependence on alcohol or other psychoactive substances, or current exposure to medications or substances with substantial effects on sleep or central nervous system function, including antidepressants or central stimulants.Presence of secondary insomnia attributable to other organic diseases.Pregnancy or breastfeeding status.History of needle syncope or presence of skin damage at the intended acupuncture sites.Known allergy to metals, including acupuncture needles.Current participation in another clinical study.

#### Termination criteria

2.6.4

Trial termination may be considered under any of the following circumstances:

Occurrence of serious safety concerns.Evidence of futility of trial continuation due to insufficient clinical benefit.Occurrence of major protocol errors or substantial deviations in trial conduct that compromise scientific validity.Discontinuation requested by the sponsor or investigator for operational reasons, including funding or management constraints.Suspension or termination mandated by the relevant regulatory or administrative authority.

### Randomization and blinding

2.7

Eligible patients with CID will be randomly assigned 1:1 to the treatment or control group. An independent statistician not involved in recruitment, intervention, outcome assessment, or data analysis will generate the randomization sequence. Allocation will be concealed in sequentially numbered, opaque, sealed envelopes. After baseline assessment, a research assistant not involved in outcome assessment or data analysis will open the next envelope and assign the participant.

Treatments will be delivered in separate sessions to reduce contamination. Acupuncturists cannot be blinded because the procedures differ, but participants will not be informed of the study hypothesis or expected superiority of either intervention. Outcome assessors and statisticians will remain blinded throughout the trial. Accidental unblinding will be documented.

### Intervention

2.8

Licensed acupuncturists with at least 5 years of clinical experience will receive standardized training before trial initiation. Both groups will receive the same conventional acupuncture prescription: Sishencong (EX-HN1), Anmian (EX-HN22, bilateral), Shenmen (HT7, bilateral), Sanyinjiao (SP6, bilateral), Shenmai (BL62, bilateral), and Zhaohai (KI6, bilateral). Detailed acupoint locations are shown in Table 2 and Figure 2. Treatment will include 12 sessions over 4 weeks, three sessions per week. In the treatment group, ultrasound-guided SG acupuncture will be performed first, followed immediately by conventional acupuncture; after all needles have been inserted, needles will be retained concurrently for 30 min.

**Table 2 tab2:** Locations of selected acupoints.

Acupoint	Location
Sishencong (EX-HN1)	Located on the head, at four points situated 1 cun anterior, posterior, and lateral to Baihui (GV20).
Anmian (EX-HN22)	At the halfway point between Fengchi (GB20) and Yifeng (SJ17)
Shenmen (HT7)	Located on the anterior wrist region, at the ulnar end of the transverse crease of the palm, on the radial side of the tendon of the flexor carpi ulnaris.
Shenmai (BL62)	Located in the ankle region, directly inferior to the prominence of the lateral malleolus, in the depression between the lower border of the lateral malleolus and the calcaneus.
Zhaohai (KI6)	Located in the ankle region, inferior to the prominence of the medial malleolus, in the depression along the lower border of the medial malleolus.
Sanyinjiao (SP6)	Located on the medial aspect of the lower leg, 3 cun superior to the prominence of the medial malleolus, posterior to the medial border of the tibia.

cun: proportional bone (skeletal) cun. Baihui (GV20): located on the head, 5 cun directly superior to the midpoint of the anterior hairline. Fengchi (GB20): located in the posterior cervical region, inferior to the occipital bone, in the depression between the upper portion of the sternocleidomastoid muscle and the upper portion of the trapezius muscle. Yifeng (SJ17): located in the neck region, posterior to the earlobe, in the depression anterior to the inferior aspect of the mastoid process.

